### Specific Aim 1 – To evaluate the differences in functional performance and subjective outcomes between non-articulating ESR, articulating ESR, and active plantarflexion ESR feet.

Hypothesis 1.1 Subjects will demonstrate improvement and preference for articulating ESR and active plantar flexion ESR feet over the non-articulating ESR feet for community mobility, particularly for those that regularly negotiate inclines and declines.

Hypothesis 1.2 Active plantar-flexion ESR feet will result in better performance metrics for mobility based outcome measures.

Hypothesis 1.3 Subjects will have decreased low back and proximal joint pain scores as determined by the visual analog scale within the Prosthetic Evaluation Questionnaire (PEQ) when using the active plantarflexion ESR foot.

Hypothesis 1.4 There will be no significant differences in functional outcome measures within all tested non-articulating ESR feet regardless of specific foot assigned.

Hypothesis 1.5 There will be no significant differences in functional outcomes within all articulating ESR feet tested regardless of specific foot assigned.

### Specific Aim 2– To evaluate the kinematic and kinetic differences of non-articulating ESR, articulating ESR, and active plantar flexion ESR feet in individuals with transtibial amputation

Hypothesis 2.1 Plantarflexion forces (i.e. ground reaction forces) at push off /terminal stance will be most symmetrical to the intact limb for active plantarflexion devices, followed by non-articulating ESR feet, and lastly articulating ESR devices.

Hypothesis 2.2 Biomechanical symmetry in gait while negotiating a decline will be greater for both active plantarflexion ESR and articulating ankle ESR conditions compared to non-articulating ESR feet.

Hypothesis 2.3 Biomechanical symmetry in gait while negotiating an incline will be greatest for devices with active plantarflexion, followed by articulating devices, and lastly non-articulating ESR feet.

Hypothesis 2.4 Ambulation at a faster than self-selected walking speed will yield decreased symmetry in articulating ankle ESR and non-articulating ESR feet but not with the active plantar flexion ESR feet.

Hypothesis 2.5 Articulating ESR feet will not yield significant differences in gait symmetry regardless of specific foot assigned within the articulating ESR category.

**Specific Aim 3 – To correlate biomechanical findings with functional and subjective outcome measures and with user preference determined through activity monitoring and user satisfaction to develop guidelines for appropriate prosthetic prescription.**

Hypothesis 3.1 Individuals that commonly negotiate ramps, hills, inclines or declines will show preference for an articulating ankle ESR and/or active plantarflexion ESR feet over non-articulating ESR feet

Hypothesis 3.2 Individuals that have higher step counts, but do so at a low activity level will prefer the active plantarflexion ESR ankle-foot prosthesis.

Hypothesis 3.3 The majority of subjects will chose to utilize a single prosthesis for all activities, and not use different prostheses for different activities, as measured through step activity monitoring and daily activity logs.

Hypothesis 3.4 Step activity performance will, and age will not, correlate with prosthetic feet category that best optimizes function.

The end point of this study is to generate findings that offer new knowledge that can be developed into clinical practice guidelines, and/or new prescription algorithms for prosthetic ankle-foot units. This information will lead to clinical prescriptions that facilitate achievement of maximal functional ability. Plainly stated, criteria will be created to assist the amputation care team in prescribing appropriate advanced prosthetic ankle-foot systems based on specific patient needs, specific patient goals, in addition to the individual current physical abilities.

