## **SAI: Data and Statistical Analysis**

*Hypothesis 1.1 Subjects will prefer articulating ESR and active plantar flexion ESR ankle-foot units over the non-articulating ESR option for community mobility, particularly for those that regularly negotiate inclines and declines.* Preference will be demonstrated in the PEQ mobility questions. Across the study population, outcomes will be assessed with descriptive statistics (i.e. means and standard errors) and compared between

each intervention prosthesis. Inferential statistics for ordinal data (SAI, HAI) will be conducted with a repeated measures Friedman test ( $\alpha=.05$ ) and a Dunn post hoc test at a 95% confidence interval. To analyze the bivariate relationships between the factors of interest and the outcome measures (SAI, HAI), t-tests will be performed.

*Hypothesis 1.2 Active plantar-flexion ESR feet will result in better performance metrics for mobility based outcome measures.* For each functional outcome measures (6-min walk, TUG, AmpPRO, SAI and HAI) we will perform a repeated-measures analysis of variance (ANOVA) to compare the 3 testing conditions. When the ANOVA reveals significant differences ( $p < 0.05$ ), we will apply pairwise comparisons using related pairs t-tests to identify the source of differences ( $p < 0.05$ ). We will compute the difference between a given pair of sessions for the subject groups and determine the mean difference for subject groups.

*Hypothesis 1.3 Subjects will have decreased pain scores as determined by the visual analog scale (VAS) within the Prosthetic Evaluation Questionnaire when using the active plantarflexion ESR ankle-foot prosthesis*

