### **SA2 Statistical Analysis:**

To address the hypotheses stated for SA2, several parameters, including temporal-spatial variables (step lengths, stance/swing times, cadence, and stride length), peak angles, moments, and powers for the ankles, knees, and hips during each phase of gait, and other biomechanical parameters (external adduction moment rate, impulse external knee adduction moment, peak vertical ground reaction force, peak resultant ground reaction force, etc.) will be measured and statistically compared across all conditions. Peak values are identified as the greatest local maxima during the first half of stance. We will use linear mixed-effects models to identify statistically significant differences in gait temporal-spatial and biomechanical variables. The fixed effects for our study will be the average differences in gait biomechanical and temporal-spatial variables by prosthetic foot type. For example, we will use a linear mixed effects regression to examine the relationship between intact knee peak EAM and prosthetic foot condition. Peak intact knee EAM will be the dependent variable, while foot condition will be the independent variable and subject by foot condition will be modeled as random effects. In the case of significance, pair-wise comparisons will be tested for significance using linear contrasts with Tukey's Honestly

Significant Difference or applying Bonferroni's correction. We will also use linear mixed effects regression to determine the association between prosthetic peak ankle power and foot condition.

### Specific Aim 3

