#### Power Analysis:

| Site                                                | n   | n for subset |
|-----------------------------------------------------|------------|---------------------|
| VA New York Harbor Healthcare System (NYC)          | 30         | 15                  |
| Walter Reed National Military Medical Center (D.C.) | 30         | 15                  |
| VA Puget Sound Healthcare System (Seattle)          | 30         | 0                   |
| James J. Peters VA Medical Center (Tampa)           | 30         | 0                   |
| TOTAL                                        | 120 | 30           |

Figure 7. Total Subjects per site to be seen over the course of 3 year period

#### Specific Aim 1

Functional measures will be analyzed by multilevel (site) repeated measures analysis of variance. Because order of prosthesis will be randomized, there should be no order effect. However, order will be included in the initial analysis to test this assumption. Assuming an alpha error rate of 5% and within-group standard deviation of 5, 120 subjects will provide over 98% power to detect a 3 unit difference between at least two of the ESR groups for each of the functional measures.

### Specific Aim 2

Kinematic and kinetic measures will be analyzed by multilevel (site) repeated measures analysis of variance. Because order of prosthesis will be randomized, there should be no order effect. However, order will be included in the initial analysis to test this assumption. Assuming an alpha error rate of 5% and within-group standard deviation of 10, 30 subjects will provide 72% power to detect a 6-unit difference between at least two of the ESR groups for each of the measures.

### Specific Aim 3

This analysis will be performed using paired t-test to determine correlations between prosthesis chosen as per SAM data and which functional outcome measures are indicative of that choice. Additionally pair t-test will be performed between kinematic and kinetic data to again correlate with the prosthetic choice of the subject as demonstrated through the SAM data. Finally all SAM data will be evaluated against the activity journal to determine the roll of a specific activity goal and a specific prosthesis.

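### Hypothesis 2.2 requires two named contrasts to hold together, so for a given symmetry variable the Tukey or Bonferroni step in Aim 2 is not needed for it and costs about 13 to 19 points of power

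*Protocol*

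**What the plan says.** Under Specific Aim 2, Hypothesis 2.2 predicts that symmetry on a decline will be "greater for both active plantarflexion ESR and articulating ankle ESR conditions compared to non-articulating ESR feet". Two contrasts are named: active plantarflexion against non-articulating, and articulating against non-articulating. The third pair, active against articulating, plays no part in it.

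The SA2 Statistical Analysis section sets one rule for all Aim 2 variables. The model is stated as "We will use linear mixed-effects models to identify statistically significant differences in gait temporal-spatial and biomechanical variables". The rule for pairs is: "In the case of significance, pair-wise comparisons will be tested for significance using linear contrasts". The adjustment named for these contrasts is Tukey's procedure or, as an alternative, Bonferroni. The section does not set the Hypothesis 2.2 contrasts apart from the other pairs, and does not say how many pairs Bonferroni would cover. Tukey by its nature covers all three.

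The Power Analysis section, Specific Aim 2, states: "Assuming an alpha error rate of 5% and within-group standard deviation of 10, 30 subjects will provide 72% power to detect a 6-unit difference". That target is a difference somewhere among the three foot groups. The section gives no within-subject correlation and no power for Hypothesis 2.2.

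**The concern.** Pairwise adjustment protects against a false finding on any one of several pairs. Hypothesis 2.2 is not of that kind: one significant contrast is not enough, because both must be shown. The need for both already limits false claims, so a stricter threshold on each contrast adds protection that this hypothesis does not need on a given variable.

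Aim 2 has only 30 subjects, and its stated power of 72% is for an easier target (a difference somewhere among the three feet). If both foot types truly help on a decline, the stricter threshold makes it more likely that the study reports the joint advantage as not shown. The protocol intends its findings to feed prescription guidelines, so such a miss has practical weight.

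**Working it through.** **Inputs from the protocol (Power Analysis, Specific Aim 2).** n = 30, SD 10, difference 6, alpha 5%, stated power 72%, three conditions. **Assumptions.** Two-sided tests; an equal correlation rho between any two feet; pooled error on (30 − 1)(3 − 1) = 58 df; for Hypothesis 2.2, true means of 0 (non-articulating), 6 and 6.

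**Step 1: the stated 72%.** For the overall repeated-measures F test on 2 and 58 df, the noncentrality is lambda = n × SS / (SD² × (1 − rho)), where SS is the sum of squared deviations of the three means.
- Means 0/6/6: mean 4, SS = 16 + 4 + 4 = 24. At rho = 0, lambda = 30 × 24 / 100 = 7.2 and power is 64%. At rho = 0.15, lambda = 720 / 85 = 8.47 and power is 72%.
- Means 0/3/6: SS = 9 + 0 + 9 = 18. At rho = 0, power is 51%. At rho = 0.36, lambda = 540 / 64 = 8.44 and power is 72%.

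So the stated inputs alone do not fix the 72%. It is reproduced at rho = 0.15 for the pattern that Hypothesis 2.2 describes, and at rho = 0.36 for evenly spaced means.

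**Step 2: false-claim rate for one variable.** The worst case is that one contrast is truly zero and the other is so large that it always passes. The joint claim is then false whenever the null contrast passes in the predicted direction, which has probability 0.05 / 2 = 2.5% for a two-sided 0.05 test. Simulation agrees: with one contrast null and the other 6 or 60 units, both passed in at most 2.5% of runs unadjusted and in about 1% with Tukey. With no differences at all, both figures were below 0.5%.

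**Step 3: power to show both contrasts.** Critical values of t on 58 df are 2.002 unadjusted, 2.405 for Tukey and 2.465 for Bonferroni over three pairs. Simulation with means 0/6/6 (100,000 or more runs per setting) gave:

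| rho | Overall test | Both, Tukey | Both, Bonferroni (three pairs) | Both, unadjusted |
|---|---|---|---|---|
| 0.15 | 72% | 39% | 36% | 55% |
| 0.36 | 84% | 55% | 52% | 71% |
| 0.50 | 92% | 70% | 68% | 83% |

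The loss from Tukey is 55 − 39 = 16, 71 − 55 = 16 and 83 − 70 = 13 points. From Bonferroni it is 19, 19 and 15 points. If each contrast uses its own paired error instead of the pooled one, the unadjusted figures are 53%, 69% and 81%.

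**Step 4: which step costs the power.** Write t1 and t2 for the two contrast statistics. With pooled error, F = (2/3)(t1² + t2² − t1 × t2). If both are at least c, the smallest possible F is (2/3)c². For Tukey this is (2/3) × 2.405² = 3.86, above the 5% critical value of F on 2 and 58 df, which is 3.16. So whenever both contrasts pass Tukey in the predicted direction, the overall test has already passed. The simulated figures with and without the overall test agree to four decimals. For unadjusted contrasts, (2/3) × 2.002² = 2.67 is below 3.16, so the overall test can bind, but it costs only about 1 point (71% to 70% at rho = 0.36). The pairwise adjustment accounts for the loss.

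**The case against.** The strongest reply is that an overall test followed by Tukey or Bonferroni is conventional and valid, and that one rule is written for all of Aim 2. Hypotheses 2.1 and 2.3 rank all three feet, so the active against articulating pair is needed there. The section also compares many gait variables and states no correction across them, so the pairwise adjustment is the only multiplicity control that it names. This stands. It is a good reason not to drop the adjustment for Aim 2 as a whole. It does not show that Hypothesis 2.2, taken on one variable, needs it.

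Some stronger readings are tempting but not supported:
- *That the plan corrects twice.* A reader might infer that the overall test and the adjustment each take power. Step 4 shows that the overall test takes none once Tukey or Bonferroni is applied.
- *That the loss is one known figure, such as roughly 69% falling to 54%.* That needs a correlation near 0.36, which matches 72% only for means 0/3/6. With 0/6/6 at that correlation the overall test has 84% power. No such figures appear in the protocol.
- *That the smaller aim is singled out for a stricter rule.* For Hypothesis 1.2 the protocol does say "we will apply pairwise comparisons using related pairs t-tests to identify the source of differences", with no adjustment. But for Hypothesis 1.3, also in Aim 1, it uses the same Tukey or Bonferroni wording, and for Hypothesis 1.1 a Dunn post hoc test.
- *That the 72% misstates the power for Hypothesis 2.2.* It is given expressly for a difference between at least two groups and makes no claim about the joint hypothesis.

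**Conclusion.** The point holds as a matter of efficiency. The rule is conservative, not invalid. For a single symmetry variable, Hypothesis 2.2 can be tested by its two contrasts at two-sided 0.05, both required, with a false-claim rate of at most about 2.5% in the predicted direction. The Tukey step lowers that to about 1% and costs 13 to 16 points of power; Bonferroni over three pairs costs 15 to 19.

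These sizes rest on 30 subjects, SD 10, a true gain of 6 units for both feet, and an assumed correlation of 0.15 to 0.5. The anchor closest to the protocol is 0.15, where power for the joint claim is 39% with Tukey and 55% unadjusted. Even without adjustment, the joint claim is less well powered there than the 72% stated for an overall difference. The Bonferroni figures further assume that it covers three pairs. The argument is made per variable; it does not settle error across the many variables that could represent symmetry.

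**What to change.** In the SA2 Statistical Analysis section, add that Hypothesis 2.2 is tested by the two named contrasts against the non-articulating foot, each at two-sided 0.05 without Tukey or Bonferroni, and is supported for a variable only if both are significant in the predicted direction. Leave the existing pairwise rule in place for the other Aim 2 comparisons.

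The cost is one or two sentences and no new data. The per-variable false-claim rate for Hypothesis 2.2 rises from about 1% to about 2.5%. Simultaneous intervals for these two contrasts become secondary. Multiplicity across gait variables remains a separate matter, which this change neither solves nor worsens beyond that per-variable rise.

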**Procedure:** During each experimental session, subjects will walk at 3 speeds across a 10 meter instrumented walkway until 5 trials when each foot makes full contact with each force plate for at least two sequential foot strikes. Since kinetic outcome measures are speed dependent, subjects will ambulate with controlled speeds determined by normalizing to each subject's intact limb length (41). Subjects will walk at their defined median Froude speed (FR3) and at one speed below and one speed above the median (FR2 & FR4), respectively. Auditory feedback will be provided to the subject in the form of a tone to ensure that they are walking at the correct speed. Subjects will be asked to repeat the walking trials until 5 acceptable trials for each speed are collected. The main purpose of this session is to collect joint motion data, force, torque, and power on subjects during each test condition. Segment ranges of motion, velocities and accelerations, and corresponding hip, knee, and ankle joint moments of force and generated/absorbed powers will be computed using inverse dynamics methods. Averages, maximum and minimum values, standard deviations and coefficients of variation will be computed for the values attained per gait cycle over each trial and for each set of trials. Spatial and temporal parameters, such as stride and step lengths, step times and velocities will also be recorded.

Additionally subjects in this subset will perform ramp ascent and descent under the collection of kinematic data. This will be performed on a standardize ramp of 1:6 rise:run ratio, which is steeper than ADA guidelines. Subjects will be instructed to ambulate at a comfortable self-selected walking speed. This will include 5 trials ascending and 5 trials descending.

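### Hypothesis 2.4 is a foot-by-speed question about faster than self-selected walking, but level-ground speeds are set by limb length and the stated Aim 2 analyses have no speed term, so they do not test it

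*Protocol*

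**What the plan says.** Three parts of the protocol bear on this.

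- **The hypothesis** (Specific Aim 2, Hypothesis 2.4): "Ambulation at a faster than self-selected walking speed will yield decreased symmetry in articulating ankle ESR and non-articulating ESR feet". The sentence goes on to exempt the active plantarflexion feet.
- **The level-ground procedure** (Gait Analysis, Procedure): "subjects will ambulate with controlled speeds determined by normalizing to each subject's intact limb length". The speeds are three: "Subjects will walk at their defined median Froude speed (FR3) and at one speed below and one speed above the median". They are enforced: "Auditory feedback will be provided to the subject in the form of a tone to ensure that they are walking at the correct speed". In the gait sessions, self-selected pace appears only for the ramp trials: "Subjects will be instructed to ambulate at a comfortable self-selected walking speed". Those trials use one pace and collect kinematics only.
- **The analysis**. SA2 Statistical Analysis says: "The fixed effects for our study will be the average differences in gait biomechanical and temporal-spatial variables by prosthetic foot type". In its worked example on the intact knee, "foot condition will be the independent variable and subject by foot condition will be modeled as random effects". The Aim 2 part of the Power Analysis section says: "Kinematic and kinetic measures will be analyzed by multilevel (site) repeated measures analysis of variance". It adds order to the initial analysis, and gives 72% power for a 6-unit difference between at least two foot groups with 30 subjects, SD 10 and alpha 5%.

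**The concern.** Hypothesis 2.4 says that going faster costs symmetry in two foot categories and not in the third. The quantity of interest is therefore how much the speed effect differs between feet. A model whose only fixed effect is foot type estimates average differences between feet. It gives no estimate of the speed effect and none of how that effect varies by foot.

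The reference speed is a separate problem. Nothing in the protocol links FR3 to a subject's usual pace, so FR4 may lie below, at or above it. A result at FR4 cannot be read as a result at faster than self-selected speed.

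At stake is one named Aim 2 hypothesis, in the 30-subject subset, whose result is meant to feed the prescription criteria. If the plan is followed as stated, Hypothesis 2.4 goes unanswered or has to be answered by an analysis chosen later.

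**Working it through.** **Step 1. Hypothesis against procedure.**

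| Element | Hypothesis 2.4 needs | Protocol provides |
|---|---|---|
| Reference speed | Self-selected, level ground | None; FR3 is set by limb length |
| Faster speed | Above self-selected | FR4, one step above FR3; relation to own pace unknown |
| Repeated speeds within each foot | Yes | Yes: five acceptable trials at each of three speeds, after each acclimation period |

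The multi-speed data exist. The self-selected reference does not.

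**Step 2. Hypothesis against model.** Write S for the symmetry measure. For the active foot (A) and one passive category (P), Hypothesis 2.4 concerns

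(S at fast speed − S at reference speed) in A, minus the same difference in P.

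This is a foot-by-speed interaction contrast. The terms the protocol names are foot type, subject by foot condition (random), site and order. None of them yields this contrast.

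**Step 3. The protocol's own 72%.** Inputs from the Power Analysis section: n = 30, difference 6, SD 10, alpha 5% (taken as two-sided for the t-tests in Step 4). For a three-level repeated-measures ANOVA with within-subject correlation ρ (not stated), the noncentrality is λ = n·Σ(μ − mean)² / [SD²(1 − ρ)].

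- Means 0, 3, 6: Σ = 18, so λ = 30 × 18 / [100(1 − ρ)] = 5.4/(1 − ρ). Power is 51% at ρ = 0 and 97% at ρ = 0.7; 72% needs ρ of about 0.36.
- Means 0, 0, 6: Σ = 24, so λ = 7.2/(1 − ρ). Power is 64% at ρ = 0 and 99% at ρ = 0.7; 72% needs ρ of about 0.15.

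The figure can be reached only by supplying a correlation that the protocol does not give, so it can be neither confirmed nor refuted. In either case it refers to a difference between feet, not to a difference in speed effects.

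**Step 4. Power of the contrast that Hypothesis 2.4 needs (illustration).** Assumptions: n = 30, 6 units, cell SD 10, a common correlation ρ between all of a subject's cells, two-sided 5% noncentral t with 29 degrees of freedom, no multiplicity correction.

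- Simple foot contrast (two cells): SD of difference = 10·√[2(1 − ρ)].
- Interaction contrast (four cells): SD = 2 × 10·√(1 − ρ).
- Noncentrality = 6·√30 / SD = 32.86 / SD.

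| ρ (assumed) | SD, simple | Power, simple | SD, interaction | Power, interaction |
|---|---|---|---|---|
| 0 | 14.1 | 61% | 20.0 | 36% |
| 0.3 | 11.8 | 77% | 16.7 | 48% |
| 0.5 | 10.0 | 89% | 14.1 | 61% |
| 0.7 | 7.7 | 98% | 11.0 | 83% |

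Under a common correlation the interaction contrast always has √2 times the SD of the simple one, so its power for the same 6 units is lower throughout.

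**The case against.** The strongest reply is that the procedure is sound and the data are adequate. The protocol gives its reason for controlling speed: kinetic measures depend on it. Free pace could differ between feet and confound the foot comparison. With five trials per speed per foot, the change in symmetry with rising speed can be estimated for every foot. This stands. A reader might infer that Hypothesis 2.4 cannot be tested at all. That goes too far: a closely related question, framed in Froude speeds, can be tested with what is collected.

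A second reply is that model terms are often left to an SAP, that the one-predictor model is offered only as an example, and that SA2 Statistical Analysis promises comparison across all conditions. This carries some weight. But the sentence on fixed effects is not part of the example and names foot type alone, and the only condition that section names is the foot. An SAP that added speed would be extending the model stated here. It could not supply a level-ground self-selected reference that is not collected.

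A reader might also infer that the team intends to test each foot separately and read a non-significant change in the active foot as no change. The wording of Hypothesis 2.4 leaves room for that error, but no passage plans it. The stated follow-up is linear contrasts between conditions with a Tukey or Bonferroni correction. An error rate built on separate within-foot tests would therefore describe an analysis the protocol does not propose, and the 72% could not serve as its input because it belongs to a different contrast.

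**Conclusion.** The concern holds as a mismatch of hypothesis, procedure and model. Hypothesis 2.4 is set against self-selected speed and is an interaction. Level-ground speeds are fixed by limb length, and the stated Aim 2 analyses contain no speed term. Those analyses do not test Hypothesis 2.4. This conclusion rests on the text and depends on no calculation.

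The defect is confined to one of five Aim 2 hypotheses and can be repaired with data already planned. The 36% to 83% power range is illustrative. It assumes the protocol's 6 units and SD 10 apply to each foot-by-speed cell, and a common correlation of 0 to 0.7 that the protocol does not state. If two speeds in the same foot are much more strongly correlated than two feet are, the disadvantage of the interaction shrinks or could reverse. Correcting for the two contrasts would lower the figures. What is firm is that the stated 72% does not describe the power for Hypothesis 2.4.

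**What to change.** 1. Reword Hypothesis 2.4 as the change in symmetry from FR3 to FR4 (or across FR2 to FR4), smaller in the active foot than in each passive category.
2. In SA2 Statistical Analysis, fit foot, speed and foot-by-speed as fixed effects, with random subject and subject-by-foot terms. Carry the same terms into the Aim 2 paragraph of the Power Analysis section.
3. Judge Hypothesis 2.4 by the interaction contrasts, active versus articulating and active versus non-articulating, each with a 95% confidence interval and the multiplicity correction already planned. Do not judge it by comparing significance within each foot.
4. State that the 72% is for a difference between foot groups and does not apply to this interaction. Give the interaction's power under stated correlations, or call the test exploratory.

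The cost is protocol wording and two model terms (speed and foot-by-speed), with no new trials or visits. The 6-minute walk should not be used as the missing reference: the protocol describes it as the distance a person can cover and ties it to functional capacity, not to usual pace. If the sponsor wants to keep the self-selected wording, level-ground self-selected speed would have to be recorded, and that would add to the gait session.
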